## Methods

The study employs a cluster randomised controlled trial designed to comply with the CONSORT guidelines [25]. Cluster randomisation is used because, although managers participate in the CLiAC program individually, they work together at a site to ensure effective aged care is delivered, so the aged care site must be the unit of randomisation. The study is set in urban and rural residential and community aged care services within two states in Australia, New South Wales (NSW) and the Australian Capital Territory (ACT), over three years. The participating research partner is one of the largest aged care service providers on the eastern seaboard of Australia, employing over 4,000 staff across NSW and the ACT. The partner organisation recognised the importance of providing a work environment that optimised staff well-being and increased capacity for high quality, safe care. Clinical leadership for middle management was identified as an area of improvement for the organisation. The organisation agreed to collaborate with the research team in researching these concepts. The collaboration is designed to provide the organisation with the opportunity to build staff capacity in these specific research areas through education/training and practice development. Mutual partnership goals include development of leadership strategies and policies that address workforce recruitment and retention in the aged care sector, which are both considered to be key to progressing high-quality care services.

### Hypotheses

The trial consists of two arms: intervention and control. Managers at the intervention sites agreed to receive the CLiAC program. At the control sites, managers agreed to provide usual care services during the study. The primary hypotheses are that, compared to the control sites, managers and staff at the intervention sites will report an enhanced work environment for staff (H_1_); and improved care quality and safety for care recipients (H_2_); and will have reduced staff turnover rates (H_3_). Secondary hypotheses include that, compared to the control sites, the intervention sites will report: reduced staff absenteeism (H_4_), improved staff ‘intention to stay’ and decreased ‘intention to leave’ (H_5_), reduced stress levels in aged care staff (H_6_), increased job satisfaction for aged care staff (H_7_), reduced costs of retaining and recruiting staff (H_8_), and improved managers’ knowledge and skills in leadership and management (H_9_).

### Ethical considerations

Prior to participant recruitment, research ethics approval was granted by the collaborating organisation’s ethics committee (HREC Code: EC00432), which was then ratified by the Human Research Ethics Committee at the University of Sydney (Database No.13405).

### Participants and sampling frame

Participants are both the care staff and the middle managers of the targeted residential and community aged care services. The sample size calculation was based on the primary outcome, participants’ perceived work environment: the subscales of the Work Environment Scale-R (WES-R) [26]. The study has 80% power to detect a difference of 0.49 standard deviations between groups as significant at the 5% level. This assumes that at least 20 clusters (sites) each with a minimum of 30 participants will complete the study, and that the intra-cluster correlation coefficient (ICC) is 0.26 (average estimate from a recent nursing home staff training intervention carried out in England and Wales) [27], giving a design effect of 8.54. The detectable difference is consistent with the WES-R [26] test developer’s recommendation that half a standard deviation represents a meaningful change on the instrument ([name], personal communication, Dec. 4, 2008). Consequently, the study will be able to detect a meaningful difference between the trial groups, and it is practical and feasible in terms of study design and data collection.

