**Methods:**

Twenty-four residential and community aged care sites were recruited as managers at each site agreed in writing to participate in the study and ensure that leaders allocated to the control arm would not be offered the intervention program. Sites undergoing major managerial or structural changes were excluded. The 24 sites were randomly allocated to receive the CLiAC program (intervention) or usual care (control), stratified by type (residential vs. community, six each for each arm). Treatment allocation was masked to assessors and staff of all participating sites. The objective is to establish the effectiveness of the CLiAC program in improving work environment, workforce retention, as well as care safety and quality, when compared to usual care. The primary outcomes are measures of work environment, care quality and safety, and staff turnover rates. Secondary outcomes include manager leadership capacity, staff absenteeism, intention to leave, stress levels, and job satisfaction. Differences between intervention and control groups will be analysed by researchers blinded to treatment allocation using linear regression of individual results adjusted for stratification and clustering by site (primary analysis), and additionally for baseline values and potential confounders (secondary analysis). Outcomes measured at the site level will be compared by cluster-level analysis. The overall costs and benefits of the program will also be assessed.

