Step 2. The lead study investigator attended a study-briefing meeting with senior managers from each eligible site to provide detailed information about the study and requirements of participating services. It was emphasised during the meeting that recruitment to the study did not guarantee that the service/site would receive the intervention program. However, the participating services were advised that if they were randomly allocated as a control site, they would be offered the CLiAC intervention after the study has been completed.

Step 3. Following the study-briefing meeting, sites were randomly selected from the eligibility list and invited to take part in the study until a total of 12 RACFs and 12 CACSs agreed to participate.

A total of 24 sites were recruited to allow for the possibility of up to four intervention sites being disqualified from the study. Sites were disqualified from the study if: all the managers of an intervention site did not participate in the CLiAC program or withdrew from the study; or a senior manager at an intervention site moved on, and their replacement did not support the intervention (this excludes a case in which a new senior manager did not want to participate in the CLiAC program while supporting the program in principle).

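### The stated 80% power for 0.49 SD does not follow from the plan's own inputs: 20 sites of 30 staff at ICC 0.26 detect about 0.67 to 0.71 SD, and power at 0.49 SD is about 50%

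*Protocol article*

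**What the plan says.** The sample size paragraph of the protocol article (Participants and sampling frame) bases the calculation on the subscales of the Work Environment Scale-R and claims: "The study has 80% power to detect a difference of 0.49 standard deviations between groups as significant at the 5% level". It gives these assumptions: "at least 20 clusters (sites) each with a minimum of 30 participants will complete the study", and "the intra-cluster correlation coefficient (ICC) is 0.26", "giving a design effect of 8.54". It then compares 0.49 SD with the instrument developer's view that half an SD is a meaningful change, and concludes: "Consequently, the study will be able to detect a meaningful difference between the trial groups".

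Two other places fix what 20 sites means. The abstract (Methods) says the 24 sites were allocated "stratified by type (residential vs. community, six each for each arm", which is 12 per arm. Recruitment of targeted aged care sites says: "A total of 24 sites were recruited to allow for the possibility of up to four intervention sites being disqualified from the study". Subtracting four from 24 leaves the 20 sites used in the power calculation, so 20 counts both arms together.

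The Data analysis plan makes the primary comparison at Time 3 a linear regression adjusted for type of care and for clustering by site. Baseline values enter only in secondary analyses.

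**The concern.** With an ICC of 0.26, the number of sites drives precision almost entirely, and 20 sites in total is few for a half-SD target. The paragraph prints both its inputs and its result, so the result can be checked, and it looked too favourable.

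This is the outcome on which the trial was sized, and the Discussion names it as the primary outcome. If power at half an SD is near 50% rather than 80%, a real benefit of the size the article calls meaningful would be missed about half the time. Readers of a null result would have a printed assurance that such a benefit should have been found.

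**Working it through.** **Inputs, all from the article:** 20 sites in total, m = 30 per site, ICC = 0.26, 5% level, 80% power, difference 0.49 SD, equal allocation of 24 sites. Sidedness is not stated. I take two-sided and test one-sided below. No gain from covariates is assumed, because the sample size paragraph states none.

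**Step 1, the design effect.** 1 + (m − 1) × ICC = 1 + 29 × 0.26 = 8.54. This reproduces the article's figure.

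**Step 2, the detectable difference with 10 sites per arm.**
- Effective staff per arm: 10 × 30 / 8.54 = 35.13.
- SE of the difference, in SD units: √(2/35.13) = 0.2386.
- Normal approximation: (1.960 + 0.842) × 0.2386 = 0.668 SD.
- Noncentral t on 18 cluster degrees of freedom: 0.707 SD.

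**Step 3, power at 0.49 SD.** 0.49/0.2386 = 2.054, and Φ(2.054 − 1.960) = 0.537. With t on 18 df it is 0.494. At 0.50 SD the normal figure is 0.554.

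**Step 4, other readings.** The SE is √[(8.54/30) × (1/k₁ + 1/k₂)], with k₁ and k₂ sites per arm.

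| Sites per arm | Detectable difference, normal / t | Power at 0.49 SD, normal / t |
|---|---|---|
| 10 and 10 | 0.668 / 0.707 | 54% / 49% |
| 8 and 12 (four intervention sites lost) | 0.682 / 0.721 | 52% / 48% |
| 10 and 12 (two sites lost, as in Trial status) | 0.64 / 0.67 | 57% / 53% |
| 12 and 12 (no loss) | 0.610 / 0.639 | 61% / 58% |
| 10 and 10, one-sided 5% | 0.593 / 0.617 | 66% / 63% |
| **20 and 20** | **0.473 / 0.485** | **83% / 81%** |

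Only the last row comes near the stated figure, and its t value of 0.485 rounds to 0.49. It needs 40 sites and 1,200 staff. The likely slip is that the trial total was entered as the number per arm. That is an inference from the match; the article does not say so.

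**Step 5, could more staff per site help?** As m grows without limit, the SE tends to √(ICC × (1/k₁ + 1/k₂)). For 10 and 10 this is √(0.26 × 0.2) = 0.228, giving 2.802 × 0.228 = 0.639 SD. For 12 and 12 it is √(0.26/6) = 0.208, giving 0.583 SD. Neither reaches 0.49.

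**Step 6, what would make 0.49 SD true with 10 sites per arm?**
- An ICC of about 0.12 (normal) or 0.11 (t) instead of 0.26; or
- covariates explaining 1 − (0.49/0.668)² = 46% of the variance of site means (52% with t). For a single site-level covariate such as the baseline mean, that is a correlation of about 0.68 to 0.72.

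**Step 7, the direct route.** Individual randomisation would need 2 × (2.802/0.49)², rounded up to 66 per arm. Multiplying by 8.54 gives 563.6 per arm, and 563.6/30 = 18.8, so 19 sites per arm by the normal approximation. With t, 19 per arm gives 79% power and 20 per arm gives 81%.

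**The case against.** The best objections concern how the calculation is framed.

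- **The split.** The disqualification rules apply only to intervention sites, so the planned 20-site case is 8 versus 12 rather than 10 versus 10. This is right, but it makes matters slightly worse (0.68 / 0.72 SD).
- **Floors.** The site and staff numbers are minima, and Trial status reports 22 sites remaining. This also stands: the trial as it ran is nearer 53% to 57% than 50%. The floor on staff cannot help, by Step 5.
- **Adjustment.** The primary model is adjusted for type of care, and the randomisation was restricted on size, span of control and location, so some between-site variance might be removed. That is possible, but about half would have to go. The article applies the full 0.26 without any such assumption, and that ICC comes from a nursing home study, so it is not obviously inflated by differences between residential and community care.
- **Reading of a null result.** The article does not say how one would be interpreted, so misreading is a risk rather than something planned.
- **Timing.** All surveys are already collected, so the correction cannot alter recruitment. It can still alter what is claimed.

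None of these restores 80%. The conflict lies between figures printed in one paragraph, so a fuller analysis plan could not remove it.

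**Conclusion.** The power statement is wrong as written. On the article's own inputs, 20 sites detect 0.67 SD (normal) to 0.71 SD (t) with 80% power, and power at 0.49 SD is 49% to 54%. The claim is overstated by roughly 26 to 31 percentage points. At the reported 22 sites, power is 53% to 57%; at the full 24, it is 58% to 61%. The conclusion that a meaningful difference can be detected falls with it.

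This assumes two-sided testing, equal site sizes, the stated ICC, and no variance removed by the type-of-care term or other covariates. One-sided testing does not change the conclusion.

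**What to change.** Replace the power sentence with one that matches its inputs, for example: *With 20 sites in total, 30 staff per site and an ICC of 0.26, an analysis not adjusted for baseline has 80% power at the two-sided 5% level for a difference of 0.67 SD (0.71 SD with t critical values) if the sites are evenly split, and 0.68 SD (0.72 SD) if they split 8 and 12; power for 0.49 SD is about 50%.* Add the figures for the 22 sites that remained.

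Delete the sentence concluding that a meaningful difference can be detected, or re-base it on an analysis adjusted for the site baseline mean, with the assumed correlation between Time 1 and Time 3 site means stated. About 0.7 is needed with 20 sites. It would also help to say that the confidence interval will be read against 0.5 SD, so that a null result is not taken as ruling out a meaningful effect.

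Restating and deleting cost wording only, with a less favourable printed figure and no extra sites. Making the baseline-adjusted analysis primary is more than wording, since the Data analysis plan now lists it as secondary. That decision should be made and documented before the analyst is unblinded. Trial status says analysis had not yet begun.

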### Recruitment of targeted aged care sites

Primary study recruitment focused on engaging targeted aged care services to take part in the study and agreement to random allocation of sites to one arm of the study. Secondary study recruitment involved: recruitment of managers at intervention sites to take part in the CLiAC program (and complete evaluation surveys) and recruitment of care staff to complete evaluation surveys; and recruitment of managers and care staff at the control sites to complete evaluation surveys.

Recruitment and follow-up of targeted aged care sites occurred between February 2011 and August 2013 and involved the following three steps:

Step 1. The central executive management of the targeted aged care services provided the research team with a list of eligible services and their contact details based on the site selection criteria (Table 1). A letter was sent to all senior and middle managers of the eligible sites informing them about the study and inviting them to participate.

**Table 1 T1:** Eligibility criteria for the recruitment of aged care study sites and participants

**Recruitment focus**	**Inclusion criteria**	**Exclusion criteria**
**Study sites: aged care services**	1. Principal support for the study is granted in writing from the Executive Care Manager or Community Manager at each site;	1. Sites which are currently (or in the near future will be) undergoing major management/structural changes.
	2. The Executive Care Managers or Community Managers at each site agree in writing that participating managers from their sites who have been allocated to the control group will not receive the intervention program during the study.	
**Participants: middle managers & care staff**	1. Currently work in a permanent middle management or in a direct care role for the participating aged care organisation;	1. Staff involved in non-direct care roles (*e.g*., administration, domestic staff, maintenance, chaplain).
	2. Have been employed by the participating organisation for a minimum of six months;	
	3. If employed in community aged care services, they must be involved in the delivery of aged cared packages including extended aged care at home (EACH), EACH-D (dementia), and community aged care packages;	
	4. Provide consent to take part in the study.	

Step 2. The lead study investigator attended a study-briefing meeting with senior managers from each eligible site to provide detailed information about the study and requirements of participating services. It was emphasised during the meeting that recruitment to the study did not guarantee that the service/site would receive the intervention program. However, the participating services were advised that if they were randomly allocated as a control site, they would be offered the CLiAC intervention after the study has been completed.

Step 3. Following the study-briefing meeting, sites were randomly selected from the eligibility list and invited to take part in the study until a total of 12 RACFs and 12 CACSs agreed to participate.

A total of 24 sites were recruited to allow for the possibility of up to four intervention sites being disqualified from the study. Sites were disqualified from the study if: all the managers of an intervention site did not participate in the CLiAC program or withdrew from the study; or a senior manager at an intervention site moved on, and their replacement did not support the intervention (this excludes a case in which a new senior manager did not want to participate in the CLiAC program while supporting the program in principle).

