### Data analysis plan

Baseline data will be analysed descriptively by allocated group. All data will be analysed on an intention-to-treat basis (*i.e*., participants will be assigned to the site where they were employed at randomisation even if they subsequently moved to another participating site). Analyses will be performed by an analyst who was not involved in data collection and is blinded to group identification, using either SAS (SAS Institute, Cary, NC, USA) or Stata (StataCorp LP, College Station, TX, USA), and supervised by a biostatistician ([name]).

For the primary analysis, differences between intervention and control groups in the primary outcome at Time 3 will be analysed using linear regression models adjusted for stratification by type of aged care (RACF/CACS) and clustering by site. Other outcomes, such as those for H_2_ and H_3_, which are measured at the cluster level, will be compared by cluster-level analysis, for example, using a negative binomial model stratified by type. All outcomes will similarly be compared at Time 2 to determine the short-term effect of the intervention. In secondary analyses, potential confounders, both at the cluster and individual level, will also be adjusted for, including baseline values of the outcome variables. Potential individual-level confounders include age, gender, previous aged care training/education, and length of time participants have worked in aged care.

An economic evaluation of the CLiAC program will be undertaken using the costs and outcomes (consequences) data discussed above. The first task will involve identifying, measuring and valuing the relevant costs and consequences of the intervention and usual practice (control group). The total costs include the cost of the CLiAC program facilitator, expert education consultant, and educational material. Quantities of resource use will be measured and unit costs (prices) will be assigned, including the cost of mentoring the CLiAC facilitator and implementing the program, using current pay rates (see HR data provided by collaborating organisation) and commercial rates (prices). The outcomes to be explored in the evaluation are: (a) the scores on the work environment measure (WES-R), effectiveness of leadership style (MLQ), person-centred care (P-CAT), and workforce dynamics (WDQ) assessed by staff; and (b) staff turnover and absenteeism. All outcomes (consequences) will be measured in natural units.

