### Trial status

We are currently in the process of completing data collection. All manager and staff surveys have been collected. We are finalising collection of the final round of Human Resource and clinical indicator data. It is expected that data cleaning and analysis will begin in the next month and will be finalised by December 2013. Two of the 24 sites were disqualified after Time 2 based on Rule 1. So far, on average, 81% of manager surveys and 41% of staff surveys have been returned.

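### Sites are disqualified after randomisation only in the intervention arm, for not taking up the program, which conflicts with the stated intention-to-treat analysis

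*Protocol article*

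**What the plan says.** The section on recruitment of aged care sites gives two grounds for disqualification. The first reads: "Sites were disqualified from the study if: all the managers of an intervention site did not participate in the CLiAC program or withdrew". The second applies where "a senior manager at an intervention site moved on, and their replacement did not support the intervention". Both name intervention sites only, and both turn on uptake or support of the program after allocation. The same section explains the number of sites: "A total of 24 sites were recruited to allow for the possibility of up to four intervention sites being disqualified from the study". The section on participants and sampling frame bases power on at least 20 sites completing.

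The data analysis plan states: "All data will be analysed on an intention-to-treat basis". Its explanation is that "participants will be assigned to the site where they were employed at randomisation even if they subsequently moved to another participating site". This covers staff who change site and does not mention disqualified sites. The primary comparison is at Time 3, by linear regression adjusted for type of care and clustering by site.

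The trial status section reports: "Two of the 24 sites were disqualified after Time 2 based on Rule 1". It adds that all surveys are in and that the last round of human resource (HR) and clinical-indicator data is still being finalised. The analyst is to be blind to group until the main analysis is complete.

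**The concern.** Intention-to-treat in a cluster trial means that each randomised site is analysed in its allocated arm, whether or not it took up the program. A rule that removes whole sites for non-uptake, in one arm only, undoes part of the randomisation. A control site with the same departures or the same indifference among its managers stays in, because nothing exists there to decline.

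The loss is unlikely to be random with respect to outcome. The Background links poor leadership to high staff turnover and ties leadership to job satisfaction and quality of care. Sites where no manager took part may well have a poorer work environment and higher turnover, which are primary outcomes. Removing them from the intervention arm alone would then favour the program.

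There is a smaller consequence for blinding. If the data set holds 10 sites in one coded group and 12 in the other, an analyst who knows the published rule can tell which group is which.

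**Working it through.** **1. Does the plan count disqualified sites as lost?** 24 recruited − 4 allowed for = 20, which equals the number of completing sites in the sample size statement. The sizing therefore treats disqualified sites as not contributing.

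**2. Which arm lost the two sites?** The article does not number its rules. Rule 1 is taken to be the first one listed. Since both rules name only intervention sites, either reading leaves 12 − 2 = 10 intervention sites against 12 control sites at Time 3.

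**3. Shift from leaving the sites out.** Let R be the mean of the retained intervention sites, D the mean of the dropped ones, and d = R − D, with sites weighted equally. The mean of all 12 is (10/12)R + (2/12)D, so dropping two sites moves the arm mean by R − [(10/12)R + (2/12)D] = (2/12)d.

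| Assumed d (SD) | Shift (SD) |
|---|---|
| 0 | 0 |
| 0.3 | 0.05 |
| 0.5 | 0.08 |
| 0.8 | 0.13 |

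Against the half SD that the article calls meaningful, 0.05 is a tenth and 0.13 about a quarter.

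**4. What range of d is plausible?** The documents give no value, but the planning assumptions bound it. The design effect reproduces: 1 + 29 × 0.26 = 8.54. The SD of a site mean with 30 respondents is √(8.54/30) = 0.53 individual SD. A simulation under no true effect (40,000 runs, 12 against 12 sites, t-test on site means) dropped the two intervention sites lowest on a compliance score that correlates ρ with site outcome. The implied gap is 12/2 times the bias.

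| ρ | Bias (SD) | Implied gap d (SD) | Two-sided type I error |
|---|---|---|---|
| 0 | 0.002 | about 0 | 4.9% |
| 0.3 | 0.044 | 0.26 | 5.4% |
| 0.5 | 0.074 | 0.44 | 6.4% |
| 1.0 | 0.146 | 0.88 | 11.3% |

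Even if the two sites lost were exactly the two worst, the expected gap is about 0.88 SD. A range of 0.3 to 0.8 SD therefore runs from modest to very strong selection.

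**5. Does keeping the sites cost precision?** With detectable difference = 2.80 × √[(8.54/30)(1/k₁ + 1/k₂)]:
- 12 against 12 sites: 2.80 × √(0.2847 × 0.1667) = 0.61 SD
- 10 against 12 sites: 2.80 × √(0.2847 × 0.1833) = 0.64 SD

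Keeping them costs nothing in nominal precision. The same formula gives 0.67 SD for 10 against 10 sites, so the article's 0.49 SD does not reproduce with 20 sites in total. That is a separate matter and does not bear on this point.

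**6. Dilution.** If retained sites gain 0.49 SD and the two non-participating sites gain nothing (an assumption), the intention-to-treat effect is 0.49 × 10/12 = 0.41 SD.

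**The case against.** The strongest reply is that the article never says the data of disqualified sites are left out. Disqualification from the study could mean only that follow-up stopped, the 20 completing sites could be an ordinary allowance for loss, and the intention-to-treat sentence covers all data. This stands in part: exclusion is an inference. But the 24 − 4 = 20 sizing points that way, and the one explanation of intention-to-treat given does not bring disqualified sites back. If they were meant to stay in, the article still has to say so.

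Several stronger readings do not hold:

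- **A large bias is established.** A reader might take d = 1.0, giving a shift of 0.17 SD, or assume four lost sites, giving 0.33 SD. A gap of 1.0 exceeds the 0.88 expected from perfect selection of the worst two sites under the article's own intra-cluster correlation. Surveys are complete and two sites were lost, so the four-site case did not arise, and four was a recruitment allowance.
- **The direction is certain.** The article does not say why the managers did not take part. If uptake is unrelated to outcome, there is no bias.
- **The analyst is unblinded.** This needs the sites to be dropped and the analyst both to see the group sizes and to know the rule. It is possible but not shown.
- **Stratification is ruined.** Unequal counts do not invalidate adjustment for type of care, and the type and location of the two sites are not given.
- **Power is seriously harmed.** The plan allowed for 20 sites and 22 remain. The change from 0.61 to 0.64 SD is minor.

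**Conclusion.** The point holds as a conflict within the article. A rule that acts on one arm only and depends on uptake after allocation has been applied to two randomised sites before the primary comparison, and on its natural reading this contradicts the intention-to-treat statement.

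The size is moderate and conditional: about 0.05 to 0.13 SD, probably in favour of the program, if retained intervention sites differ from the dropped ones by 0.3 to 0.8 SD. That range is an assumption, and the shift disappears if uptake and outcome are unrelated. Disclosure of the arms through 10 against 12 sites is a risk and not an established fact. The point needs correcting before the main analysis, because the article itself fixes the rule and reports its use.

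**What to change.** State that the two sites discontinued the program but not the study, and that the primary analysis includes every randomised site in its allocated arm with all available data. For these two sites that means:

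- HR data, which the HR section says the organisation supplies for each site over the whole study, and clinical-indicator data, which belong to its routine collection. Final collection is still under way, so gaps can be requested now.
- Time 1 and Time 2 surveys, which should exist because the sites left after Time 2.
- Time 3 surveys, if they were collected.

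Keep the stated Time 3 regression as the primary model; this point gives no reason to replace it with a repeated-measures model. If Time 3 surveys are absent for these sites, add a sensitivity analysis that varies their missing site means over a stated range. Report the 22-site comparison separately, labelled as per-protocol. Holding all 24 sites in the data set also keeps the coded groups equal in number of sites wherever data exist.

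The cost is a change of wording, a small data request to the organisation and some dilution of the estimate by non-adherent sites, which is what an intention-to-treat estimate is meant to reflect.
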